### Sample size

#### Assumptions

For the purposes of the power calculation, the proportion of participants self-harming within the two groups has been chosen as the primary outcome, as this is likely to be the most consistent across the data collection methods, the most complete, and is more amenable to cost-effectiveness analysis. In a previous large RCT (the POPMACT trial) of cognitive therapy versus TAU for people who self-harmed, 36% of patients in the TAU group had a self-harm episode over the first 6 months of the trial [24]. We envisage that the incidence of self-harm in our TAU will be similar to the POPMACT trial. In an RCT of 'green cards' versus TAU for first presentation self-harm, the risk of self-harm after randomisation in the green card group was 37% (95%CI 14% to 97%) of the risk in the TAU group [25]. Given that the green card is not individualised whereas JCPs will be, it will be assumed that the JCP intervention would result in a larger effect, with a lower proportion (one third) of individuals at risk of self-harm since randomisation (33%).

#### Power calculation

Participants will be followed up for a minimum of six months with a predicted 36% and 12% of participants repeating self harm (including serious threats) in the TAU group and JCP intervention group respectively. On the basis of these predictions, an overall sample of 114 (randomised 1:1 to TAU: JCPs) would provide 80% power to detect an observed difference between TAU and JCPs based on a 2-sided test at the 5% significance level. This will be increased to 120 to allow a small loss in the administrative data on self-harm. This sample is also large enough to provide 80% power to detect a constant hazard ratio between the groups of 0.29 with proportions of events in the two groups as stated above, based on the log-rank statistic assuming no accrual rate, a fixed time of follow-up and an estimated 10% dropout.

### Statistical analysis plan

An intention-to-treat analysis will be applied in the first instance (i.e. analysing all available data from randomised participants). The three data collection methods for the outcome of self-harm (i.e., participant interviews, diaries and electronic case records) are likely to differ on the amount of missing data. We will compare proportions of missing data using chi-square tests and agreement between data collection methods using Lin's Concordance Correlation Coefficient. Preliminary effectiveness estimates: Logistic regression will be used to compare proportions of patients that have self-harmed during the follow-up period in the two groups. Analysis of 'time to first self harm' outcome will also be conducted using survival analysis methods; log-rank test for bivariate comparisons and cox's proportional hazards to adjust for gender, stratification variables and time spent on treatment prior to randomisation. Other outcome assessments (continuous and binary) will be compared between the treatment groups at 6-month follow-up using t-tests, chi-square tests or non-parametric equivalents as appropriate, and regression modelling. The primary outcome analysis will be repeated on all three outcome collection methods to determine if conclusions remain the same. We expect little disparity in reporting of 'any self-harm episode' but potentially more in the time of first episode and number of episodes. If conclusions differ by the collection method used we will investigate reasons for the discrepancy. From this analysis we will be more certain of the appropriate collection methods for self-harm data and be better placed to decide on the appropriate outcome measure and estimate effectiveness in a future definitive trial.

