The treatment of people with BPD is frequently characterized by conflicts with health professionals and such conflicts are particularly likely to arise in the management of self-harming behaviour [11]. Moreover, the cessation of self-harming behavious is often associated with an individual's ability to assert greater control over their life [12]. Given that the JCP is designed to facilitate a more collaborative relationship with staff, we hypothesise that JCPs may be an effective way of managing self-harm in people with BPD. In this article, we describe the proposed methods of an exploratory randomized controlled trial (RCT) that is designed to estimate the effectiveness and cost-effectiveness of JCPs on self-harming behaviour in people with BPD and to determine the most effective methods of data collection to inform future studies.

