### Self-harm follow-up data

Variables (i) and (ii) will be gathered from the following sources:

1. The follow-up interviews with participants at 6-months - participants will be asked to recall the approximate number of self-harm events occurring over the preceding six months. Variables (iii) and (iv) will be gathered using questions derived from Hawton et al [15].

2. Diaries: all participants will be supplied with a simple diary/calendar and will be asked to record all self-harm events on this (by simply circling the days of the month on which self-harm events occurred).

3. Electronic psychiatric case records.

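### Missing-data rates from three sources on the same participants are to be compared by chi-square tests with no paired form named, and the diary and interview counts are in different units (minor)

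*Protocol article*

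**What the plan says.** The Background gives, as one purpose of the trial, "to determine the most effective methods of data collection to inform future studies". The Statistical analysis plan section serves it in three ways. The first two stand in one sentence: "We will compare proportions of missing data using chi-square tests and agreement between data collection methods", with Lin's concordance coefficient as the only agreement statistic named. The third is a repeat of the primary analysis on each source.

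The three sources share one set of people. Under Self-harm follow-up data, "all participants will be supplied with a simple diary/calendar and will be asked to record all self-harm events". Follow-up assessments states that every participant is followed up at six months. The section on randomisation and minimising bias adds that records are also used for people lost to the interview.

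The units differ. The diary is filled in "by simply circling the days of the month on which self-harm events occurred", whereas at interview "participants will be asked to recall the approximate number of self-harm events occurring over the preceding six months".

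**The concern.** Each participant contributes up to three missing/not-missing indicators. An ordinary chi-square test on the source-by-missing table treats them as 360 independent observations (240 for a pair of sources). The same person failing to provide both interview and diary is the obvious case in which they are not independent. The section names no paired test, and where it mentions chi-square tests again, for outcomes between the arms, the ordinary test is clearly meant.

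For the count, the diary can record at most one per day, while the interview has no such ceiling. Lin's coefficient, unlike a correlation, falls when one measure is systematically larger than the other. Part of any shortfall would then come from the form of the question and not from poor recall or recording.

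At stake is the quality of the evidence for choosing a collection method for the definitive trial. The Discussion notes that no gold standard exists for measuring self-harm, so this comparison carries some weight.

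**Working it through.** **Inputs.** n = 120 randomised (Power calculation section). The article's 114 reproduces as 57 per arm for 36% v 12% with a continuity correction; it is not in dispute and only leads to n. The article gives no missing-data rates or overlaps, so those below are assumptions.

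**1. One example, two sources.** Suppose 24 and 36 of 120 are missing.

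- Unpaired: pooled proportion 60/240 = 0.25; X² = (24 − 36)²/(240 × 0.25 × 0.75) = 144/45 = 3.20, p = 0.074. This is the same whatever the overlap.
- Paired: with s people missing on both, the discordant counts are 24 − s and 36 − s, and exact McNemar is a two-sided binomial test with probability 0.5 on them.

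| Missing on both (s) | Discordant split | Exact McNemar p |
|---|---|---|
| 7 (about what independence gives: 24 × 36/120 = 7.2) | 17 v 29 | 0.104 |
| 12 | 12 v 24 | 0.065 |
| 16 | 8 v 20 | 0.036 |
| 20 | 4 v 16 | 0.012 |
| 24 | 0 v 12 | 0.0005 |

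The paired test gains only when overlap is clearly above chance.

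**2. Type I error of the unpaired test.** With equal missingness p and within-person correlation φ, the variance of the difference in proportions is 2p(1 − p)(1 − φ)/n, but the test uses 2p(1 − p)/n. The real type I error is therefore about 2[1 − Φ(1.96/√(1 − φ))].

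- p = 0.25, half of the missing shared: φ = (0.125 − 0.0625)/0.1875 = 0.33; 1.96/√0.667 = 2.40; error 1.6% (1.7% in simulation).
- φ = 0.5, which needs 62.5% shared: 1.96/√0.5 = 2.77; error 0.6%.

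**3. Three sources, simulated (4,000 trials per setting, 120 people).**

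| True missing | φ | Unpaired chi-square rejects | Cochran's Q rejects |
|---|---|---|---|
| 25/25/25% | about 0 | 5.1% | 5.1% |
| 25/25/25% | 0.39 | 0.5% | 5.1% |
| 20/30/20% | about 0 | 45% | 45% |
| 20/30/20% | 0.37 | 39% | 64% |
| 20/30/20% | 0.54 | 36% | 81% |
| 15/30/5% | 0 to 0.50 | about 100% | 100% |

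The loss is material for moderate differences and absent for large ones.

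**4. Days v events.** Let X be self-harm days and suppose that both sources are free of error, with events Y = kX. Then the correlation is 1, but Lin's coefficient = 2k/[1 + k² + (k − 1)²/CV²], where CV is the SD of X divided by its mean. With CV = 2 (assumed, for skewed counts):

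- k = 1.5: 3/(3.25 + 0.0625) = 0.91
- k = 2: 4/(5 + 0.25) = 0.76
- k = 3: 6/(10 + 1) = 0.55

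With CV = 1 the values are 0.86, 0.67 and 0.43. Two perfect sources would thus appear to disagree.

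**5. Lin's coefficient on a yes/no variable.** It can be written as 1 − E(X − Y)²/[var X + var Y + (difference in means)²]. On 0/1 data the numerator is the probability of disagreement, and the denominator reduces to p₁ + p₂ − 2p₁p₂, the disagreement expected by chance. That is Cohen's kappa. In 2,000 simulated data sets the two differed by at most 1e-15.

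**The case against.** **McNemar and Cochran's Q are themselves referred to a chi-square distribution, so a condensed article may have meant them.** That is possible. But nothing in the text points to a paired form, and followed as written it gives the ordinary test.

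**The error is on the safe side and may be small where records are involved.** This largely stands. Under positive correlation the test is conservative and the missing proportions themselves do not change. Records are sought even for people lost to interview, and the Power calculation section expects only a small loss there. Overlap with records may therefore be low and gaps large, where both tests do equally well. The loss of power is plausible mainly for interview v diary. Negative correlation would make the unpaired test anti-conservative; the article gives no figure either way.

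**Lin's coefficient is meant to penalise systematic shifts, and the article expects more disparity in the number of episodes.** True, but the coefficient cannot separate a shift built in by the unit from under-recording, and only the latter informs the choice of method.

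Two stronger readings are tempting and should not be made. A reader might infer that Lin's coefficient misstates agreement on the yes/no outcome. The article does not say to which self-harm variable it applies, and on 0/1 data it equals kappa. A reader might also infer that sources are matched on statistical significance. The text speaks only of conclusions, and its stated response is to look into differences: "If conclusions differ by the collection method used we will investigate reasons for the discrepancy". Chance rates of discordant significance between sources therefore do not count against this plan.

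**Conclusion.** The point holds as a minor one, in two parts.

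First, as written, the test for missing data ignores pairing. The size depends on assumed rates and overlap. In the 24 v 36 example, p is 0.074 unpaired against 0.012 with 20 people missing on both, but there is no gain when overlap is near chance. At 25% missing with half shared, the type I error is about 1.7% instead of 5%. With 20/30/20% missing and φ of 0.37, power is 39% against 64%.

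Second, the diary and interview counts are in different units, so Lin's coefficient for the count would be low even with perfect reporting (about 0.76 at two events per self-harm day, with the assumed spread of CV = 2).

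It would go too far to say that the choice of method will come out wrong. Descriptive completeness is unaffected, large differences are still found, and the choice also draws on repeating the analysis by source. The randomised comparison and the sample size are untouched, and the Discussion states that the trial is not definitive.

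**What to change.** - **Missing data:** replace the chi-square tests with Cochran's Q across the three sources, followed by McNemar for pairs, or use a logistic GEE clustered on participant. Report the paired differences in proportion missing with confidence intervals. The cost is wording only.
- **Counts:** compare sources in like units. Ask at interview for the number of days with self-harm as well as the number of events, reduce dated record entries to days where possible, and apply Lin's coefficient to the count only on that scale. The cost is one extra interview question. It must be in place before the follow-up interviews, because events cannot be turned into days afterwards, nor diary days into events.

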### Randomisation procedure and methods to minimise bias

Participants will be randomised using the method of minimisation with a random component stratified by alcohol misuse [as measured by the Alcohol Use Disorders Identification Test (AUDIT) [13]] and depression [as measured by the Hospital Anxiety and Depression Scale (HADS) [14]]. The randomisation will be managed by the Clinical Trials Unit (CTU) at the Institute of Psychiatry. Confirmation of eligibility, consent, and baseline data will be obtained prior to randomisation. Bias in the recruitment and randomisation process will be avoided by having randomisation done centrally by the CTU, and hence concealment maintained from the investigators, and by keeping a log of all service users randomised and including them all in the analysis. The research worker collecting outcome data will be blinded to the allocation. Some outcome data will be obtained from electronic patient records, even for participants lost to follow-up interview. This will include any episodes of self harm, hospital admissions and service use recorded in the electronic records. Bias in the collection of outcome data will also be minimised by the use of standardised objective assessments and by blinding the researchers as far as possible to service user allocation. There will be specific instructions to participants and clinical teams not to disclose the treatment details of any study participant. Every effort will be made to maximise the single blindness of research workers, whose 'best guesses' of treatment arm status will be assessed after the final assessment in order to test whether their blindness was successfully maintained.

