#### Follow-up assessments

Six months after randomisation, all participants will be followed-up. A research worker, blinded to treatment allocation, will arrange a convenient time to meet with the participant in order to complete the following measures:

i) Time to first act of self-harm (if any)

ii) Number of self-harm episodes over the preceding 6-month period

iii) Regarding the most recent act of self-harm - length of time from contemplation of self-harm to self-harm act

iv) Regarding the most recent act of self-harm - help-seeking behaviour prior to event (see 10.3)

v) WAI-S (client + therapist)

vi) WSAS

vii) Service Engagement Scale

viii) Treatment Experience Scale

ix) EQ-5D

x) CSQ

xi) ADSUS

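### The chi-square tests named for comparing missing data between interview, diary and electronic records ignore that all three sources come from the same participants (minor)

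*Protocol article*

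**What the plan says.** The Statistical analysis plan section expects that the three ways of collecting self-harm data "are likely to differ on the amount of missing data", and then states: "We will compare proportions of missing data using chi-square tests and agreement between data collection methods". Agreement is to be measured with Lin's concordance coefficient. No paired test or model clustered by participant is named for missingness.

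Three places show that each source is sought for each person:

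- **Interview** (Follow-up assessments): "Six months after randomisation, all participants will be followed-up".
- **Diary** (Self-harm follow-up data): "all participants will be supplied with a simple diary/calendar". The list of sources there is introduced by "Variables (i) and (ii) will be gathered from the following sources", the variables being time to first self-harm and number of episodes.
- **Records** (Randomisation procedure and methods to minimise bias): "Some outcome data will be obtained from electronic patient records, even for participants lost to follow-up interview".

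Later in the Statistical analysis plan section the same test name is applied to independent arms: other outcomes "will be compared between the treatment groups at 6-month follow-up using t-tests, chi-square tests or non-parametric equivalents as appropriate".

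**The concern.** A Pearson chi-square test for comparing proportions takes the groups to be independent samples. Here the groups are three measurements on one set of people. Someone who loses contact with the study is likely to miss the interview and also fail to return the diary. That shared cause makes missingness in those two sources positively correlated, and the Pearson variance has no term for it.

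What is at stake is a methodological aim. The article gives finding the best way to collect self-harm data as a purpose of this exploratory trial, and completeness is one of the two source comparisons it names, the other being agreement. A test with the wrong variance could report sources as no different in completeness when a moderate difference exists.

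**Working it through.** **The plan's own figure.** The article gives no number for the missing-data comparison. Its sample size was reproduced to confirm that it is separate from this point. Inputs from Power calculation: 36% v 12%, two-sided 5%, 80% power.

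- Uncorrected: n = [1.960·√(2·0.24·0.76) + 0.842·√(0.36·0.64 + 0.12·0.88)]² / 0.24² = 48.5, so 49 per arm.
- Continuity-corrected: (48.5/4)·[1 + √(1 + 4/(48.5·0.24))]² = 56.5, so 57 per arm, or 114 in total as stated.

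The increase to 120 is also stated: "This will be increased to 120 to allow a small loss in the administrative data on self-harm". Nothing in this calculation depends on how missingness is compared.

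**Size of the variance error.** Let two sources have the same proportion missing p in n people, with within-person correlation φ. The difference has variance 2p(1−p)(1−φ)/n. The Pearson test uses 2p(1−p)/n. The true standard error is therefore √(1−φ) times the one used: 0.84 at φ = 0.3, 0.71 at φ = 0.5 and 1.10 at φ = −0.2.

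For three sources with equal rates and a common φ, the Pearson statistic behaves as (1−φ) times a chi-square on 2 degrees of freedom. A nominal 5% test then has true size 0.05^(1/(1−φ)). At φ = 0.284 this is 0.05^1.397 = 1.5%.

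**Simulation.** Assumptions: 120 participants, 10,000 replicates, and correlated missingness generated from a latent normal variable with a common correlation across the three sources. The missing rates and φ are assumed, because the article gives neither. Entries are the percentage of replicates significant at 5%.

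| True missing rates | φ (approx.) | Pearson | Cochran's Q |
|---|---|---|---|
| 20/20/20 | −0.13 | 7.9 | 5.7 |
| 20/20/20 | 0 | 5.4 | 5.3 |
| 20/20/20 | 0.17 | 3.0 | 5.0 |
| 20/20/20 | 0.28 | 1.3 | 4.9 |
| 20/20/20 | 0.44 | 0.4 | 5.0 |
| 20/30/20 | 0 | 45 | 45 |
| 20/30/20 | 0.17 | 43 | 52 |
| 20/30/20 | 0.29 | 41 | 60 |
| 20/30/20 | 0.45 | 39 | 72 |
| 20/40/5 | any tried | about 100 | about 100 |

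The simulated sizes lie within a percentage point of the closed form.

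**One pair by hand, as an upper bound.** Assume 18 of 120 interviews (15%) and 30 of 120 diaries (25%) are missing.

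- Pearson: 0.10² / (0.20·0.80·2/120) = 3.75, p = 0.053. Unpaired standard error: √(0.15·0.85/120 + 0.25·0.75/120) = 0.0512.
- If all 18 people without an interview also have no diary, the discordant counts are 12 and 0. Paired standard error: √((12 − 12²/120)/120²) = 0.0274. Exact McNemar p = 2·0.5¹² = 0.0005.
- The ratio of standard errors is 0.0512/0.0274 = 1.87.

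This is the extreme case. φ = (0.15 − 0.15·0.25)/√(0.15·0.85·0.25·0.75) = 0.73 is the largest correlation those margins allow, and only one of the three pairs is involved.

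**The case against.** **The wording may not exclude a paired test.** McNemar's test and Cochran's Q are also referred to a chi-square distribution, the article is condensed, and Lin's coefficient in the same sentence does use the pairing. This is a fair point: that the data would be handled as 360 unrelated observations is an inference, not a stated fact. The Pearson reading is still the natural one, because the section uses the same unqualified name for independent arms.

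**Records may behave differently.** They are obtained even for people lost to interview, and only a small loss is expected. Correlation with the other two sources may be weak and the difference in completeness large. The two comparisons involving records may then be little affected. This stands, and it limits the point mainly to interview v diary.

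**No decision hangs on the p-value.** The observed percentages missing are unbiased whichever test is used, no rule selects a source on this test, and the choice also draws on agreement and on repeating the primary analysis in each source. This stands too, and is why the point is minor.

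**Stronger readings to avoid.** A reader might infer that the plan's confidence intervals are wrong, but none is planned for this comparison. A reader might infer that real differences will be missed; that needs both positive correlation and a moderate difference. Nor does anything here support doubt about the treatment effect.

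**Conclusion.** The point holds as a minor one. The three proportions are paired by design, and an ordinary chi-square test has the wrong variance whenever missingness is correlated across sources. The direction depends on the sign of the correlation: conservative if positive, too liberal if negative, unaffected at zero.

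Under the assumed 20/30/20 rates, power falls short of Cochran's Q by about 9 percentage points at φ near 0.17 and 19 at φ near 0.29. These figures rest on assumed rates, a common correlation across all three sources, and the Pearson reading of the text. The effect stays within the comparison of collection methods; the treatment analyses and the sample size are untouched.

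**What to change.** In the Statistical analysis plan section, replace the chi-square tests for the missing-data comparison with Cochran's Q across the three sources. Add pairwise McNemar tests (exact where discordant counts are small) and paired confidence intervals for the differences in proportion missing. If a paired test was intended all along, naming it is enough to settle the test, and the paired intervals can be added in the same sentence. The chi-square tests between treatment arms stay as they are.

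The cost is one sentence. No new data are needed, and at zero correlation power is essentially unchanged (45% for both tests in the 20/30/20 case).

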### Assessments

#### Baseline assessments

(i) Socio-demographic details - age, sex, ethnicity, employment, educational, marital status

(ii) Details of self-harming behaviour over the preceding 6 months - measured using questions from Hawton et al [15]

(iii) Personality disorder status - Structured Clinical Interview for DSM-IV personality disorders (SCID-II) [16] - BPD subsection

(iv) Functional impairment - Work & Social Adjustment Schedule (WSAS) [17]

(v) Engagement with services - Service Engagement Scale [18]

(vi) Working Alliance - Working Alliance Inventory- Short Form (client version) (WAI-S) [19]

(vii) WAI-S (therapist version)

(viii) Health-related quality of life - Euroquol (EQ-5D) [20]

(ix) Satisfaction with care - Client Satisfaction Questionnaire (CSQ) [21]

(x) Perceived coercion - Treatment Experience Scale [22]

(xi) Service use - Adult Service Use Schedule (ADSUS) [23]

(xii) Alcohol use - Alcohol Use Disorders Identification Test (AUDIT) [13]

(xiii) Illicit substance use - Questionnaire on use of illicit substances taken over last year

(xiv) Emotional symptoms - Hospital Anxiety and Depression Scale (HADS) [14]

Additionally, socio-demographic data and length of practice data will be collected for care coordinators, using a proforma developed during the previous pilot work.

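### The minimisation factors are named as covariates for the Cox model only. The main logistic model and the comparisons of the scales should also name them, with the baseline values already collected.

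*Protocol article*

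**What the plan says.** All places are in the protocol article.

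- **Allocation** (Randomisation procedure and methods to minimise bias): "minimisation with a random component stratified by alcohol misuse", measured by AUDIT, and by depression, measured by HADS.
- **Outcome that sized the trial** (Sample size, Assumptions): "the proportion of participants self-harming within the two groups has been chosen as the primary outcome".
- **Its analysis** (Statistical analysis plan): "Logistic regression will be used to compare proportions of patients that have self-harmed during the follow-up period in the two groups". No covariate is named.
- **Time to first self-harm** (same section, next sentence): a log-rank test, then a Cox model to "adjust for gender, stratification variables and time spent on treatment prior to randomisation".
- **Other outcomes** (same section): "Other outcome assessments (continuous and binary) will be compared between the treatment groups at 6-month follow-up using t-tests, chi-square tests". The sentence goes on to allow non-parametric tests and adds regression modelling, without saying which covariates enter.
- **Baseline data** (Baseline assessments): "Details of self-harming behaviour over the preceding 6 months", and also WAI-S, WSAS, Service Engagement Scale, Treatment Experience Scale, EQ-5D and CSQ. All six scales are repeated at 6 months (Follow-up assessments).
- **Economics** (Economic evaluation): costs are compared by t-test, with ordinary least squares for adjusted analyses. QALYs are to be based on the EQ-5D, and no adjustment is mentioned for them.

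**The concern.** Two models of the same self-harm data stand in adjacent sentences. One lists its covariates, including the factors used in allocation, and the other lists none. The section gives no reason for the difference.

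Minimisation removes between-arm variation due to AUDIT and HADS from the treatment estimate. An analysis that leaves the factors out still counts that variation in its standard error. If the factors predict self-harm, the interval is then too wide and the test falls below its nominal level. Leaving out a measured baseline value also leaves chance imbalance uncorrected, in a trial of 120.

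This matters here because the first aim includes estimating the likely range of effects, and the results are meant to inform a definitive trial. Interval width is therefore one of the trial's main products.

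**Working it through.** **1. The plan's own figures.** The Power calculation gives "a predicted 36% and 12% of participants repeating self harm (including serious threats) in the TAU group and JCP intervention group respectively", and says "an overall sample of 114 (randomised 1:1 to TAU: JCPs) would provide 80% power" on a two-sided 5% test.

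- Pooled rate (0.36 + 0.12)/2 = 0.24. Uncorrected n per arm = [1.96·√(2·0.24·0.76) + 0.842·√(0.36·0.64 + 0.12·0.88)]² / 0.24² = 48.5, so 49 per arm or 98 in total.
- With the continuity correction: (48.5/4)·[1 + √(1 + 4/(48.5·0.24))]² = 56.5, so 57 per arm. This gives 114, an exact match.
- 114/0.95 = 120, the stated target.
- ln(0.88)/ln(0.64) = 0.286, which agrees with the stated hazard ratio of 0.29.

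The figures reproduce, and they come from an unadjusted comparison of two proportions. Without the continuity correction, power is about 86% at 57 per arm and 88% at 60. This is why the simulated powers below start near 89%, not 80%.

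**2. Any self-harm: simulation.** The article gives no prognostic strength, so these inputs are assumptions: two independent binary minimisation factors (50% prevalence each), binary baseline self-harm (60%), an 80% biased coin, N = 120, and 3,000 runs per setting. All three covariates share one conditional odds ratio (OR). Type I error was simulated at 36% in both arms, and power at 36% v 12%.

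| Assumed OR | Type I error, no covariates | Type I error, two factors | Power, no covariates | Power, two factors | Power, factors + baseline self-harm |
|---|---|---|---|---|---|
| 1 | 5.5% | 5.5% | 89.1% | 89.6% | 89.5% |
| 2 | 4.2% | 5.0% | 88.6% | 89.6% | 90.2% |
| 3 | 4.0% | 5.3% | 89.3% | 90.9% | 91.4% |
| 5 | 2.9% | 4.6% | 88.3% | 91.6% | 93.6% |

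- Simulation error is about √(0.05·0.95/3000) = 0.4 points for the type I figures.
- Power lost by leaving out the two factors is 0.5 to 3.3 points. Leaving out baseline self-harm as well costs 0.4 to 5.3 points.
- Under the null, the unadjusted model's standard error against the true spread of its estimate is 0.385 v 0.374 (OR 2), 0.384 v 0.368 (OR 3) and 0.384 v 0.352 (OR 5). The ratios are 1.03, 1.04 and 1.09, so intervals are about 3%, 4% and 9% too wide. At OR 1 there is no such excess (0.385 v 0.396).

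**3. Scales with a baseline.** Against a t-test at 6 months, ANCOVA multiplies the variance by 1 − r², where r is the correlation between baseline and 6 months. The article does not give r, so a range is assumed.

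| r | Variance factor | Interval narrower by | Equivalent N for 120 |
|---|---|---|---|
| 0.3 | 0.91 | 1 − √0.91 = 5% | 120/0.91 = 132 |
| 0.5 | 0.75 | 1 − √0.75 = 13% | 120/0.75 = 160 |
| 0.7 | 0.51 | 1 − √0.51 = 29% | 120/0.51 = 235 |

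**4. QALYs.** If QALYs are the area under a straight line from baseline to 6 months (assumed), then QALY = 0.5·(u₀ + u₆)/2 = 0.25·u₀ + 0.25·u₆. A chance baseline EQ-5D difference of d between the arms then adds 0.25·d to the QALY difference, whatever the treatment does.

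**The case against.** The strongest reply is that this is a condensed article and that covariate lists are commonly left to a fuller plan. Much of that stands:

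- A reader might infer that the logistic model is declared unadjusted. It is not; the article only names no covariates.
- A reader might infer that the scales are compared by t-test alone. The same sentence adds regression modelling, and costs have an adjusted analysis.
- A reader might infer that every outcome has a baseline. Time from contemplation to act and help-seeking have none listed separately, and time to first episode after randomisation can have none.
- The odds ratio is non-collapsible. An adjusted logistic model estimates a conditional odds ratio, and its standard error on the log-odds scale generally does not shrink. The gain on the binary outcome is in the level and power of the test, not in a narrower interval for the same quantity.
- The trial calls its effectiveness estimates preliminary and does not claim to be definitive.

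Silence is therefore not the ground for this point. The ground is that the section does list covariates for one self-harm model and not for the other, and puts t-tests at 6 months first for scales that have a baseline. A better analysis of data already planned is available at almost no cost.

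**Conclusion.** The point holds as an improvement to the stated analysis. It is not an error that threatens validity.

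- **Binary outcome.** The effect is small and depends on the factors being prognostic. Without covariates the test is conservative (about 4% at an assumed OR of 2 to 3, 2.9% at 5) and gives up under 6 points of power, with baseline self-harm included in that count. If the factors are not prognostic, there is no mismatch.
- **Scales.** The effect can be larger if the t-test is the main analysis: intervals could be about 5% to 29% narrower for r from 0.3 to 0.7.

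A reader might go on to infer inflated false-positive risk, an underpowered trial or a wrong sample size. None follows. The direction is conservative, simulated power without covariates is already 88% to 89%, and 114 and 120 reproduce. Nor do the documents show that prior treatment time is a wrong covariate for the Cox model. It is not a separate item in the baseline list, but it may be obtainable elsewhere, and replacing it would be a matter of preference.

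**What to change.** Before unblinding, state in the analysis plan:

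1. **Any self-harm:** a logistic model with arm, the two minimisation factors (AUDIT, HADS depression) and baseline 6-month self-harm. Also report the standardised (marginal) risk difference, so that the result can be read against the 36% v 12% that sized the trial.
2. **Time to first self-harm:** add baseline self-harm to the covariates already named.
3. **WAI-S, WSAS, Service Engagement, Treatment Experience, EQ-5D, CSQ:** ANCOVA with the baseline score and the two minimisation factors as the main analysis, in place of the t-test.
4. **QALYs:** adjust the comparison for baseline EQ-5D.

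The cost is wording and a little analysis time, with no new data. Events are the limit: 60·0.36 + 60·0.12 = 28.8 are expected. The logistic model has four coefficients beyond the intercept, about 7 events each. The Cox model would have six if each covariate takes one coefficient, about 5 events each. Keep both lists short and fixed in advance, and name a penalised fit as the fallback if data are sparse. A fixed list also prevents covariates being chosen after the data are seen.
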